**Discussion:**

This study intends to compare the efficacy between MA and PA in the treatment of perimenopausal women with GAD and to further study the mechanisms underlying the effect.

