## Background

Generalized anxiety disorder (GAD) is a kind of chronic mental disorder that includes both mental and physical symptoms [1]. GAD patients have general apprehensiveness or worry that is not restricted to any particular stimulus as the primary clinical feature [2]. According to epidemic research in Europe, the incidence rate of GAD is 6.2% throughout the lifetime [3]. Moreover, females have 1.5 to 2 times more exposure to GAD than males [4]. To our knowledge, the prevalence of females aged between 45 years old and 54 years old is the highest [5]. This phenomenon indicates that perimenopausal women are more likely to suffer from GAD. As one of the first-line pharmacotherapies for GAD [6], serotonin reuptake inhibitors (SSRIs) inhibit the reuptake of serotonin to increase the concentration of serotonin in the synaptic cleft to improve the level of serotonin in the brain which is believed to attenuate anxious symptoms [7]. However, patients’ conditions might be aggravated in the first week when first taking SSRIs [8]. Therefore, some patients refuse to take drugs because of adverse events. They seek for the help of psychiatrists and some of them probably receive cognitive behavioral therapy (CBT). Studies [9, 10] have shown that CBT is an effective treatment for GAD. However, due to the shortage of professionals and high cost, CBT is not beneficial for most patients in China [11]. Therefore, patients turn to find help from alternative therapies such as acupuncture.

Although the pathogenesis of GAD is not yet clear, current studies believe that it is related to abnormal secretory function of the hypothalamic-pituitary-adrenal axis (HPA axis) [12]. Cortisol (CORT) synthesized by the adrenal cortex is one of the final products of the HPA axis. CORT and adrenocorticotropic hormone (ACTH) levels in GAD patients are higher than those in normal people [13, 14]. The elevation of CORT and ACTH is detected as negative feedback by the hypothalamus which downregulates the stress response [15, 16]. Therefore, the decline in CORT and ACTH levels could predict the degree of improvement that a treatment produces [17].

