Therefore, we designed a randomized controlled trial that focus on the efficacy of manual acupuncture (MA) versus placebo acupuncture (PA) on GAD in perimenopausal women. To evaluate the therapeutic efficacy of GAD, the primary outcome measure used in our protocol is the change in scores on the Hamilton Anxiety Scale (HAMA). The secondary outcome measures are the changes in scores on the Generalized Anxiety Disorder Scale (GAD-7) and Pittsburgh Sleep Quality Index (PQSI), and laboratory indicators related to the current possible pathogenesis of GAD, mainly including CORT and ACTH. This protocol aims to explore the efficacy of MA in GAD patients who would not prefer drug or CBT therapies. Meanwhile, we hope to explore the possible mechanism of acupuncture on GAD by measuring the levels of CORT and ACTH in serum.

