#### CORT and ACTH

It has been suggested that anxious subjects demonstrate greater CORT and ACTH concentrations [28]. In this study, we will draw serum samples and investigate CORT and ACTH before and after acupuncture. An enzyme-linked immunosorbent assay (ELISA) will be used to measure CORT and ACTH. These related tests will be carried out by the clinical laboratory of the First Affiliated Hospital of Guangzhou University of Chinese Medicine.

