## Discussion

According to recent meta-analyses or systematic reviews [29, 30], acupuncture shows to have a better treatment efficacy for GAD, but the conclusions are limited. Many articles have compared efficacy between MA and PA, but the conclusions are different. Some reviews [31–34] have concluded that MA is definitely better than PA, and other reviews [35] found no difference between MA and PA. The jury is out on whether or not there is an existing acupuncture placebo effect. To the best of our knowledge, no trial has studied the efficacy of MA versus CBT in treating GAD. In the present research [36], CBT combined with electroacupuncture (EA) resulted in a lower HAMA score than CBT or EA alone. In China, CBT is not as widespread as in Western countries. The expense of CBT is much higher than that of acupuncture, so a few GAD patients will choose CBT to treat GAD. Therefore, this trial compared MA and PA to determine whether there is a placebo effect and provide clinical evidence of the placebo effect of acupuncture.

There are many types of anxiety disorders and GAD is one of the most common types. The HAMA, introduced in 1959, was widely used in evaluating anxiety levels in lots of clinical trials. The GAD-7, introduced in 2006, was designed for GAD; this is a special type of anxiety disorder. However, RCTs about anxiety used GAD-7 as an outcome are limited. Due to the specificity of the GAD-7 and the generalization of the HAMA, we will use the HAMA scores as the primary outcome and the GAD-7 scores as the secondary outcome to measure the change in patients’ anxiety levels. We will use the PSQI scores as a secondary outcome because there is a high rate of comorbidity between insomnia and GAD [37, 38]. Less sleeping will aggravate patients’ mental burden and worsen their anxiety. Therefore, we want to determine whether there is a connection between GAD and sleeping. In addition, we will collect serum samples of GAD patients to evaluate the changes in CORT and ACTH during treatment. If the levels of CORT and ACTH are associated with the level of GAD, acupuncture may treat GAD via the HPA axis.

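### The Discussion infers an HPA-axis mechanism from an association between hormone levels and anxiety, which can arise when MA and PA have identical hormones

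*Protocol article*

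**What the plan says.** Mechanism is a declared aim. The Abstract says the trial intends "to further study the mechanisms underlying the effect", and the Background says "we hope to explore the possible mechanism of acupuncture on GAD by measuring the levels of CORT and ACTH in serum".

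The Discussion says what would support a pathway. It first states that "we will collect serum samples of GAD patients to evaluate the changes in CORT and ACTH during treatment", and then: "If the levels of CORT and ACTH are associated with the level of GAD, acupuncture may treat GAD via the HPA axis".

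Three other places bear on this:

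- **Background.** It reports that "CORT and adrenocorticotropic hormone (ACTH) levels in GAD patients are higher than those in normal people", and adds that a fall in these hormones could predict how much a treatment helps.
- **Secondary outcome, CORT and ACTH.** It states "It has been suggested that anxious subjects demonstrate greater CORT and ACTH concentrations", and for sampling: "we will draw serum samples and investigate CORT and ACTH before and after acupuncture".
- **Data monitoring and analysis.** CORT and ACTH go to a covariance analysis, with Kruskal-Wallis as the alternative. All tests are two-sided at 0.05. The section describes no analysis relating hormones to anxiety scores.

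**The concern.** The condition in the Discussion concerns how hormones and anxiety relate across patients. The conclusion concerns what acupuncture does. Nothing in the condition compares MA with PA, so randomisation does not protect the inference.

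If the sentence is followed as written, the trial could report support for an HPA-axis pathway although CORT and ACTH are the same in both arms. It could also give too little weight to the evidence that does bear on mechanism: a randomised difference in hormones, and then a link between hormone change and HAMA change.

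**Working it through.** **1. The logic.** The article gives no figure for this inference, so there is none to reproduce. Two readings of the condition are possible.

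- *Levels with levels.* If more severely ill patients have higher CORT and ACTH, levels correlate with anxiety whichever needle was used.
- *Changes with changes.* The preceding sentence in the Discussion allows this reading. If anxiety and hormones fall together in both arms, through natural course or placebo response, the changes correlate with no effect specific to MA.

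Either way, the condition can be met with an MA-PA hormone difference of exactly zero.

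**2. Illustration: inputs.**

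- From Sample size: post-treatment HAMA 14.0 (SD 3.2) for MA and 19.4 (SD 5.3) for PA; 44 per arm before allowance for withdrawal, 56 per arm enrolled.
- From Data monitoring and analysis: two-sided 0.05.
- Assumed, because the document gives none: the within-arm correlation ρ between one hormone and HAMA, here 0 to 0.4.
- Assumed: a pooled Pearson correlation as the test of association, since no such test is specified.
- Set by construction: the same hormone distribution in both arms.

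**3. Simulation, 10,000 trials per setting.** Proportion with a significant association:

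| ρ | 44/arm, HAMA effect as planned | 56/arm, HAMA effect as planned | 44/arm, no HAMA effect | 56/arm, no HAMA effect |
|---|---|---|---|---|
| 0 | 0.05 | 0.05 | 0.05 | 0.05 |
| 0.2 | 0.34 | 0.42 | 0.47 | 0.56 |
| 0.3 | 0.66 | 0.75 | 0.82 | 0.90 |
| 0.4 | 0.89 | 0.95 | 0.98 | 0.99 |

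In the same simulated trials a two-sample t-test of the hormone between arms was significant in 0.046 to 0.053.

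**4. Check by Fisher's z.** With m = atanh(r) × √(N − 3), the probability is 1 − Φ(1.96 − m) + Φ(−1.96 − m).

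- *No HAMA effect* (r = ρ). At N = 112 and ρ = 0.3: m = 0.3095 × √109 = 3.23, probability 0.90. For ρ = 0.2 and 0.4 it is 0.56 and 0.99. At N = 88 the three values are 0.46, 0.81 and 0.97.
- *HAMA effect as planned.* The arm difference adds HAMA variance unrelated to the hormone, so the pooled correlation shrinks. Covariance: ρ × (3.2 + 5.3)/2 = 4.25ρ. HAMA variance: (3.2² + 5.3²)/2 + (5.4/2)² = 19.165 + 7.29 = 26.455, SD 5.14. So r = 4.25ρ/5.14 = 0.83ρ. At ρ = 0.3, r = 0.248 and atanh(r) = 0.253. At N = 88, m = 0.253 × √85 = 2.33, probability about 0.65, against 0.66 simulated.

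The figures are per hormone. The Discussion does not say whether one or both must be associated.

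**The case against.** The strongest reply is that this is one hedged sentence in a Discussion about an exploratory aim, and that the right comparison is probably already planned. CORT and ACTH are secondary outcomes of an MA-versus-PA trial, sampled before and after treatment and assigned to a covariance analysis. The natural reading is a baseline-adjusted arm comparison, and identical hormones in the two arms should show up there. The Background also has a change-based rationale, and any exploratory association model may sit in an analysis plan that is not shown.

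Much of this stands, and it rules out several stronger readings that a reader might infer:

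- *That the trial has adopted a decision rule, or that this is its only reasoning about mechanism.* The analysis section sets no association test or threshold, and the Background offers the change-based line.
- *That the plan ignores change under treatment or has no arm contrast for the hormones.* The sentence before the inference refers to changes, and the covariance analysis could supply the contrast.
- *That the condition must already hold at baseline.* Higher hormones in GAD patients than in normal people do not establish a correlation with severity among GAD patients. Everyone enrolled has GAD, and entry HAMA is limited to 14 to 28, which would tend to weaken such a correlation.
- *That 56% to 99% is this trial's error rate.* Those figures need an assumed ρ, all 112 patients analysed, no HAMA effect and a test the article does not specify. At ρ = 0 the figure is 5%.

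The reply does not repair the inference. A hedged conclusion still needs a condition that bears on it, and the Discussion does not link its conclusion to the planned hormone comparison.

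**Conclusion.** The point holds as a fault in a stated inference. An association between hormones and anxiety, in levels or in changes, does not show that acupuncture acts through the HPA axis, because it can occur with identical hormones in MA and PA. That conclusion is logical and needs no value of ρ.

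The size is illustrative only. For ρ of 0.2 to 0.4 and no hormone effect, the association would be significant in roughly 34% to 89% of trials under the less favourable setting for detecting it (44 per arm, planned HAMA effect), and in 56% to 99% under the most favourable (56 per arm, no HAMA effect). A between-arm hormone test stays near its nominal 5%. The primary efficacy conclusion does not depend on any of this, so the severity is minor.

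**What to change.** Rewrite the sentence in the Discussion so that an HPA-axis statement is reached in steps:

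1. Require first an MA-PA difference in post-treatment CORT or ACTH adjusted for baseline, naming which hormone or hormones must show it. The planned covariance analysis serves, with arm as the factor and the baseline hormone value as the covariate.
2. Only if that difference is present, relate hormone change to HAMA change, adjusted for arm and baseline values. Label this exploratory: both changes arise after randomisation, so even this step is not proof of a pathway.
3. Report associations of hormone levels with anxiety as descriptive, with no mechanism claim.

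This uses data already being collected and changes only analysis and reporting text. The cost is a harder condition to meet before any mechanism statement can be made.

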## Trial status

The trial is currently being carried out right now and the end date of enrollment is expected on May 1, 2022.
